### Sample size

This study is designed to evaluate whether the efficacy of low-dose tamoxifen in reducing IBTR is not inferior to that of whole breast irradiation in patients with low-risk and ER-positive breast DCIS. We hypothesize that in all patients who meet the cohort 1 criteria of the ECOG E5194 study and have ER-positive status in the tumor, the 7-year IBTR rate in those who underwent BCS alone will be < 10.5% (assumption: 6–7%). In our previous study, breast DCIS patients who underwent BCS alone had the ECOG E5194 cohort 1 criteria, in whom the 7-year IBTR rate was 5% and 8% in the ER-positive and ER-negative groups, respectively [7]. For the ER-positive group tumors, most patients received tamoxifen as an adjuvant setting. Under these assumptions, we hypothesized that for low-risk breast DCIS, the 7-year IBTR rate would be approximately 6% in patients who underwent BCS alone (neither tamoxifen nor RT). The current trial was designed to evaluate whether the administration of low-dose tamoxifen (tamoxifen 5 mg for 5 years; experimental group) is not inferior in decreasing the cumulative incidence of IBTR when compared with the prescription of RT (50 Gy in 25 fractions or 40.05 Gy in 15 fractions; control group). We assume that a 6% incidence of IBTR at 7 years will be observed in participants who underwent whole breast RT alone and expect that the cumulative incidence of 7-year IBTR will not be > 6% in participants who receive low-dose tamoxifen (5 mg for 5 years).

In total, 385 patients are needed in each group to provide 90% β-power with an α type I error of 5% (margin, IBTR difference, 5%); this permits a loss of 5% of patients due to follow-up at 5 years (statistical methods are shown in Table 2). As approximately 5% of patients cannot tolerate the side effects of low-dose tamoxifen and will receive RT, we estimate that 405 patients will be enrolled in the tamoxifen arm. Therefore, 810 patients will be enrolled in this randomized non-inferiority trial. The targeted number of breast events is not described in the protocol, but the ripeness of the data from this trial will be revaluated and deliberated by Taiwanese and Japanese teams. If at least 80% of case report forms are returned 5 years after starting treatment, we will properly consolidate this trial’s corrected data.

**Table 2 Tab2:** Statistical methods

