**α: type 1 error—> 0.05**
**β: power—> 0.9**
**Assume (no-RT) low risk IBTR: 6%**
**Assume that Tamoxifen = RT = 6%**
**Assume a margin (IBTR difference: 5%)**
**N = (Z**_**α**_** + Z**_**β**_**)**^**2**^**xS**^**2**^**/Δ**^**2**^ = **385 (per arm)**
**N = 2 * n = 770 (total)**

### Recruitment

Patients will be recruited among those with breast DCIS who underwent BCS and visited the outpatient department of participating sites of the TBCC-ARO DCIS trial. In the current protocol, no advertising or inducements will be permitted and recruited. Patients will be randomized by the TBCC-developing “Clinical Study Information System” (CSIS) by logging clinicopathological information on their respective websites.

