### Assignment of interventions: allocation

#### Sequence generation

When patients meet the criteria of the current study, they will be stratified into different groups based on the pathological characteristics of their post-BCS tumor specimens (tumor size: ≤ 1 cm vs. > 1 cm; margin width: 3– < 10 mm vs. ≥ 10 mm) before randomization.

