### Statistics

#### Statistical methods for primary and secondary outcomes

In this study, patients who do not follow the protocol of their assigned treatment arm will not be analyzed. We will use the chi-square test, Student’s *t*-test, and Fisher’s exact test to compare the clinical characteristics between patients undergoing RT and those receiving low-dose tamoxifen. In this study, we will use the Kaplan–Meier method to estimate the time to IBTR (only breast area), ipsilateral regional recurrence of lymph nodes (including axillary, supraclavicular, or internal mammary lymph nodes), contralateral breast local recurrence, and distant metastases from the date of surgical excision. In addition, we will use this method to calculate overall survival, which will be measured from the date of surgical excision to the date of death from any cause or to the date of the last follow-up. Comparisons between the patients will be performed using the log-rank test. All statistical analyses will be carried out at a 5% significance level.

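### The one outcome comparison the article names, a log-rank test at 5%, does not address the 5-point margin in 7-year IBTR on which the trial is sized

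*Protocol article*

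**What the plan says.** The Sample size section states the hypothesis as one about 7-year IBTR: low-dose tamoxifen "is not inferior in decreasing the cumulative incidence of IBTR when compared with the prescription of RT". It assumes 6% in the radiotherapy arm and no more than 6% under tamoxifen. Table 2 sets the non-inferiority margin in the line that begins "Assume a margin (IBTR difference: 5" (per cent). The size follows: "385 patients are needed in each group to provide 90% β-power with an α type I error of 5" per cent.

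The section Statistical methods for primary and secondary outcomes then describes the analysis:

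- Estimation: "we will use the Kaplan–Meier method to estimate the time to IBTR (only breast area", with the same method for the other recurrence types and for overall survival.
- Comparison: "Comparisons between the patients will be performed using the log-rank test".
- Level: "All statistical analyses will be carried out at a 5% significance level". Whether this is one- or two-sided is not stated.

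The section also names chi-square, t and Fisher tests, but for baseline description: "Fisher’s exact test to compare the clinical characteristics between patients undergoing RT and those receiving low-dose tamoxifen". The log-rank test is therefore the only between-arm comparison of outcomes in the article. The margin appears in the Abstract, the Sample size text and Table 2. It does not appear in the analysis section, whether as a confidence limit, a shifted null or a hazard-ratio margin.

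**The concern.** The design asks whether 7-year IBTR under tamoxifen exceeds that under radiotherapy by less than 5 points. A log-rank test asks whether the hazards differ at all. A non-significant result may only mean too few events, and a significant result may come with a difference that lies wholly inside the margin. The trial's one confirmatory claim would then rest on a test of a different hypothesis. The tempting shortcut, treating no significant difference as non-inferiority, becomes easier as the trial gets smaller. That matters here, because Trial status reports 36 patients enrolled by December 2022 against 810 planned.

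**Working it through.** **Inputs.** From Sample size and Table 2: 6% IBTR at 7 years in both arms, margin 5 points, alpha 5%, power 90%, 385 per arm, 5% loss. From the statistical methods section: log-rank test, 5% level. Assumed here: exponential event times with proportional hazards, and a two-sided log-rank test unless noted.

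**1. The plan's own figure.** Table 2 gives N = (Zα + Zβ)² × S² / Δ². Take S² = 2 × 0.06 × 0.94 = 0.1128 and Δ = 0.05.

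- One-sided 5%, z rounded to 1.64 and 1.28: 0.1128 × 2.92² / 0.0025 = 384.7, so 385. With unrounded z it is 386.4, so 387.
- One-sided 2.5%: 0.1128 × (1.96 + 1.282)² / 0.0025 = 474.2 (475 with unrounded z). This does not reproduce 385.
- A test for any difference between 6% and 11% at 90% power would need 652 per arm (two-sided 5%) or 531 (one-sided 5%).

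So 385 is the size for a one-sided 5% non-inferiority test on a risk difference and for no test of equality.

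**2. What the log-rank test does at the margin.** Put the truth at the margin: radiotherapy 6%, tamoxifen 11%.

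- Hazard ratio = ln(0.89) / ln(0.94) = 1.883, and ln(1.883) = 0.633.
- Events = n × (0.06 + 0.11). Expected z = 0.633 × √(events / 4). P(non-significant) = Φ(1.96 − z).

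| Per arm | Events | Expected z | P(non-significant), two-sided 5% |
|---|---|---|---|
| 385 | 65.5 | 2.56 | 0.27 |
| 365 (about 5% of 385 lost) | 62.1 | 2.49 | 0.30 |
| 100 (illustration) | 17 | 1.31 | 0.74 |

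A simulation (exponential times, 7 years' follow-up, 4,000 runs) gave 0.30 at 385 and 0.77 at 100. If the 5% level were one-sided, 1.645 replaces 1.96 and the probabilities are 0.18 at 385 and 0.20 at 365, still well above 5%.

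**3. What it does under the planning assumption.** With a true 6% in both arms, a 5% log-rank test is significant about 5% of the time at any size. The planned 90% power therefore does not describe it.

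**4. The two questions can give opposite answers.** Simple binomial approximation, 385 per arm:

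- Observed 6% versus 9%: SE = √((0.06 × 0.94 + 0.09 × 0.91) / 385) = 0.01895; z = 0.03 / 0.01895 = 1.58, not significant. Upper limit = 3.0 + 1.645 × 1.895 = 6.1 points, so non-inferiority is not shown.
- Observed 1% versus 4%: SE = √((0.01 × 0.99 + 0.04 × 0.96) / 385) = 0.01120; z = 2.68, significant. Upper limit = 3.0 + 1.645 × 1.120 = 4.8 points, so non-inferiority is met.

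The second pattern needs a radiotherapy rate well below 6%. In simulations with radiotherapy at 6% it did not occur. The Background section does cite a randomized trial with a 7-year rate of 0.9% after radiotherapy.

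**5. The test that matches the sizing.** Claim non-inferiority if the upper end of the two-sided 90% interval for the difference is below 5 points. At 385 per arm and 6% in both arms, SE = √(0.1128 / 385) = 0.01712 and power = Φ(0.05 / 0.01712 − 1.645) = 0.90. The simulated error rate at 6% versus 11% was 5.7% at 385 per arm and 5.0% at 405.

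**The case against.** The strongest reply is that this is a condensed article. The margin, rates, time point, alpha and power are stated, Kaplan–Meier estimation is stated, and a confidence-limit decision rule is something that a full protocol or SAP commonly supplies. That limits what can be said about the trial's complete plan: a reader might infer that the non-inferiority hypothesis will never be tested, and the article alone cannot show that. It does not remove the mismatch, because the article does not leave the outcome comparison open. It names a test that does not fit its hypothesis, and an SAP that tested the margin would have to depart from that text. A log-rank-type test can be built with a shifted null hazard ratio, but the article states no such shift and its margin is an absolute 7-year difference.

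Three further inferences are tempting and not supported:

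- **Non-significance will be taken as non-inferiority.** No section says so. The 27% to 30% is conditional on that reading.
- **The test ignores the randomization strata** ("tumor size: ≤ 1 cm vs. > 1 cm; margin width: 3– < 10 mm vs. ≥ 10 mm"). The analysis section does not say whether the log-rank test is stratified, and that is ordinary SAP detail.
- **Hazards cannot be proportional because tamoxifen stops at 5 years.** Non-proportionality does not invalidate a log-rank test under its own null. The Discussion cites a halving of recurrence at 9.7 years' median follow-up after only 3 years of treatment, so the documents do not show that the effect ends with treatment.

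**Conclusion.** The stated analysis is wrong as written for the hypothesis that sized the trial. That conclusion needs no modelling assumption: the margin does not enter the only outcome comparison named, and 385 per arm corresponds to a different test. The size of the possible harm is conditional. If non-significance on a two-sided 5% log-rank test were read as non-inferiority, the false-claim rate at 6% versus 11% would be about 27% to 30% at 365 to 385 per arm against the intended 5%, and roughly three in four at 100 per arm. These figures rest on proportional hazards with a ratio of 1.88. It should be corrected before outcomes are analyzed, because the trial's main claim depends on it.

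**What to change.** For the IBTR non-inferiority hypothesis, replace the log-rank sentence with a rule along these lines: estimate the 7-year IBTR rate in each arm (Kaplan–Meier or cumulative incidence); report the difference, tamoxifen minus radiotherapy, with its confidence interval; declare non-inferiority only if the one-sided 95% upper limit, which is the upper end of the two-sided 90% interval, is below 5 points. State the sidedness. One-sided 5% matches the 385; at one-sided 2.5%, power at 385 falls to 83% and 90% power needs 475 per arm. Keep the log-rank test as supportive only. Combining the difference over tumor size and margin width is optional and not needed to cure the mismatch.

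State that this test applies to IBTR, and reconcile it with the Abstract and the Outcomes section, which define the primary endpoint as any breast recurrence (ipsilateral, regional, contralateral or distant).

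The cost is one paragraph in the protocol and SAP. It calls for no data item beyond those already planned: follow-up is scheduled to 10 years, and the 7-year estimate must wait until enough of it has accrued.

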**Methods/design:**

This is a prospective, international, open-label, randomized, non-inferiority trial. Patients with low-risk clinicopathologic features (> 40 years old, low risk of breast cancer susceptibility gene (*BRCA) 1* and *BRCA2* mutations, mammographically detected unicentric and non-mass lesions, low- or intermediate-grade without comedo or necrosis, measuring < 2.5 cm with margins ≥ 3 mm, and estrogen receptor-positive status) of DCIS who underwent BCS will be randomized at a 1:1 ratio to either receive tamoxifen (5 mg/day) for 5 years or undergo RT with conventional fractions (50 Gy in 25 fractions) or hypofractionations (40.05 Gy in 15 fractions). Randomization will be stratified by the Taiwan Breast Cancer Consortium. As approximately 5% of patients cannot tolerate the side effects of low-dose tamoxifen and will receive RT, we estimate that 405 patients will be randomized to a low-dose tamoxifen arm and 405 patients to the RT arm, according to a non-inferiority margin within 5% of IBTR difference and 90% β-power noticing non-inferiority. The primary endpoints are breast tumor recurrence, including ipsilateral, regional, contralateral, and distant recurrence of breast DCIS or invasive cancer. The secondary endpoints are overall survival and adverse effects of RT and tamoxifen. Translational studies will also be conducted for this trial.

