### Methods for additional analyses

In this trial, the subgroups of pathological features will be managed based on the primary and secondary endpoints stratified by tumor size and surgical margin status.

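### The between-arm comparison carries no strata although randomization is stratified by tumor size and margin width; stratifying it, and aligning the abstract, is a low-severity improvement

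*Protocol article*

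**What the plan says.** - **Randomization (Sequence generation).** Before randomization, "they will be stratified into different groups based on the pathological characteristics of their post-BCS tumor specimens". The factors are tumor size, ≤1 vs >1 cm, and margin width, 3 to <10 vs ≥10 mm.
- **Comparison (Statistical methods for primary and secondary outcomes).** Time to each type of recurrence and overall survival are estimated by Kaplan–Meier. Then: "Comparisons between the patients will be performed using the log-rank test". No strata are mentioned, and the word *unstratified* does not appear either.
- **Use of the factors in the analysis (Methods for additional analyses).** "the subgroups of pathological features will be managed based on the primary and secondary endpoints stratified by tumor size and surgical margin status". This is the only analysis in which the two factors appear.
- **Abstract (Methods/design).** "Randomization will be stratified by the Taiwan Breast Cancer Consortium". Neither size nor margin is mentioned there.
- **Sample size and Table 2.** 385 per arm, assuming 6% 7-year IBTR in both arms, a 5-point margin, type I error 5% and power 90%. The calculation contains no strata.

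**The concern.** An analysis normally reflects the way patients were randomized. If arms are balanced within strata that predict recurrence, the estimated difference varies less from trial to trial. A standard error that ignores the strata does not take credit for this. The interval is then slightly too wide, and some power can be lost. In a non-inferiority trial the upper confidence limit decides the result, so even a small unneeded width matters in principle.

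The article does more than leave the point open. It names the test, and it gives the two factors a role in the analysis, but only as subgroups. The natural reading is that the main comparison does not use them. The abstract adds uncertainty, because its one sentence on stratification does not name the factors given in the body.

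**Working it through.** **1. Reproduce the planned size.** Inputs from Sample size and Table 2: p = 0.06 in both arms, margin Δ = 0.05, α = 0.05, power 0.90. The sidedness of α is not stated.

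n per arm = (z₀.₉₅ + z₀.₉₀)² × 2p(1−p) / Δ² = (1.645 + 1.282)² × 2 × 0.0564 / 0.0025 = 386.4, so 387. The plan states 385. The figure therefore reproduces closely with one-sided α of 5% (one-sided 2.5% would give 475). It involves no strata, so stratifying the analysis does not change it.

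**2. How much variance could the strata carry?** The protocol gives no rates by size or margin cell. *Assumption:* four equal cells with 7-year IBTR averaging 6%, in three sets from mild to extreme.

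Share of variance between strata = mean of (p_k − 0.06)² / (0.06 × 0.94)

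| Assumed cell rates (%) | Mean squared deviation | Share | × 770 patients |
|---|---|---|---|
| 3, 4.5, 6.5, 10 | 0.0006875 | 1.2% | 9 |
| 2, 4, 6, 12 | 0.0014 | 2.5% | 19 |
| 1, 3, 6, 14 | 0.00245 | 4.3% | 33 |

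**3. What that means for power.** SE without strata = √(2 × 0.0564 / 385) = 0.01712, so Δ/SE = 2.921. Let f = √(1 − share). The strata are balanced, so the true standard deviation of the difference is f × SE whichever analysis is used.

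- Without strata: power = Φ((2.921 − 1.645)/f)
- With strata: power = Φ(2.921/f − 1.645)

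| Share | f | Without strata | With strata | Gain (points) |
|---|---|---|---|---|
| 1.2% | 0.994 | 90.0% | 90.2% | 0.2 |
| 2.5% | 0.988 | 90.2% | 90.5% | 0.4 |
| 4.3% | 0.978 | 90.4% | 91.0% | 0.6 |

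Simulation of the same three sets (binomial outcomes, 385 per arm, 400,000 replicates, simple Wald limits) gave gains of 0.1 to 0.5 points at the nominal cut-off. With type I error matched, the gain was about zero. The unstratified two-sided 95% interval covered 95.0% to 95.5%.

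**4. The log-rank test itself.** Simulation of 770 patients over 7 years, with 1,500 runs per setting and a two-sided 5% test. Equal cells, permuted blocks of 4 and the prognostic effects are assumptions. The hazard ratio that corresponds to 6% vs 11% is ln 0.89 / ln 0.94 = 1.88.

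| Effect of each factor | Rejection with no difference: without / with strata | Rejection at hazard ratio 1.88: without / with strata |
|---|---|---|
| None | 4.8% / 4.9% | 69.9% / 69.8% |
| Hazard ratio 2 or 1/2 | 4.7% / 5.1% | 69.5% / 70.5% |
| Hazard ratio 3 or 1/3 | 3.7% / 3.9% | 69.6% / 71.0% |

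The simulation error is about 0.5 point in the first comparison and 1.2 points in the second. The differences lie within or near it. Leaving out the strata does not inflate type I error.

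**5. Sparse cells.** 385 × 0.06 = 23.1 events per arm, and 23.1 / 4 = about 6 per stratum and arm. With about 96 patients in each, the chance that at least one of the eight stratum-arm cells has no event is 1 − Π(1 − (1 − p_k)⁹⁶)², which gives 13%, 30% and 66% for the three sets. A simple stratified Wald limit is strained here: in simulation its one-sided type I error was 5.4–5.5%, against 5.0–5.2% without strata.

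**The case against.** **The article never says the test is unstratified.** This is correct. A full protocol or analysis plan, not shown here, could specify strata. But the article fixes a test and assigns the two factors to subgroup analyses, so its text points away from a stratified comparison. A clarifying sentence is a fair request. A charge of error would not be.

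**The prognostic gradients are assumed.** This stands. The Background uses small size and wide margin to define low risk. It does not show that these cut-points separate risk among patients already limited to ≤2.5 cm and ≥3 mm. In the investigators' own cohort treated by surgery alone, the reported prognostic factors were age and estrogen receptor status. If size and margin are not prognostic here, the gain is zero.

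**Stratifying is not free.** This also stands. With about 6 events per stratum and arm, a simple stratified limit is slightly anti-conservative. Part of its apparent power gain comes from that.

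**Stronger readings that a reader might infer:**
- *The abstract names a different stratifier.* The documents do not establish this. Recruitment and Concealment mechanism place the randomization in the consortium's own web system, so the phrase may say who carries it out. With 9 consortium sites and 2 Japanese sites, a consortium factor is conceivable, but it is not stated.
- *The analysis ignores the design's blocks.* No blocking is described anywhere in the article.
- *The interval is materially too wide.* Coverage of 95.0% to 95.5% does not support that.

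**Conclusion.** The point holds as a low-severity improvement. Randomization uses two factors, the stated comparison does not, and the abstract fails to name them. The comparison without strata is valid and at most slightly conservative, and it does not bias the result. Against the 5-point margin, stratifying would gain less than 1 point of power under the assumed rates, and possibly nothing. This rests on four equal cells, 6% overall IBTR, 385 per arm, one-sided 5%, and stratum rates that the protocol does not supply. The planned number of patients is unaffected.

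Stratification should not be mistaken for a remedy to a separate matter. A log-rank test of no difference, stratified or not, does not by itself judge the 5-point margin. For that reason the stratified estimate that matters most is the 7-year difference with its confidence limit.

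**What to change.** 1. **Statistical methods for primary and secondary outcomes.** State that the between-arm comparison is stratified by the randomization factors, tumor size and margin width. This should include the 7-year IBTR difference judged against the 5-point margin. Estimate that difference as a stratum-weighted (Mantel–Haenszel type) difference, with a score-type or small-sample-corrected confidence limit.
2. **Sparse cells.** Pre-state a rule for pooling cells with too few events.
3. **Log-rank test.** Keep it, stratified by the same factors, as a supportive comparison.
4. **Abstract.** Reword the stratification sentence so that it names the same factors as Sequence generation. If consortium is in fact a factor in the randomization module, add it to Sequence generation and to the stratified analysis.

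The cost is a few sentences, with no new data or patients, plus some care over the limit and the pooling rule. With 36 of 810 patients enrolled by December 2022, this can be settled well before outcome data could influence the choice, which is worth doing in an open-label trial.

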### Outcomes

Our primary objective is to observe breast tumor recurrence, including ipsilateral, regional, contralateral, and distant recurrences of breast cancer (DCIS or invasive cancer events).

Our secondary objective is to assess overall survival in all patients, adverse effects of RT and tamoxifen, and translational studies—including single nucleotide polymorphisms (SNPs), extracellular matrix (ECM)- and immune-related molecules, and mutational analyses of selected genes.

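### Four recurrence sites are listed as primary endpoints and each is analysed at 5% with none named as decisive, although the trial is designed on ipsilateral breast tumor recurrence (IBTR) alone

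*Protocol article*

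**What the plan says.** - **Abstract, Methods/design:** the endpoint sentence reads "The primary endpoints are breast tumor recurrence, including ipsilateral, regional, contralateral, and distant recurrence of breast DCIS or invasive cancer".
- **Outcomes:** the section opens with "Our primary objective is to observe breast tumor recurrence, including ipsilateral, regional, contralateral, and distant recurrences of breast cancer (DCIS or invasive cancer events". Overall survival and adverse effects are secondary.
- **Statistical methods for primary and secondary outcomes:** the time-to-event plan begins "we will use the Kaplan–Meier method to estimate the time to IBTR (only breast area), ipsilateral regional recurrence of lymph nodes". The same sentence goes on to contralateral recurrence and distant metastases as further separate times. No composite time to any recurrence is named. On testing, it says "Comparisons between the patients will be performed using the log-rank test". The section closes with the blanket rule that "All statistical analyses will be carried out at a 5% significance level".
- **Sample size:** the opening sentence gives the purpose as "This study is designed to evaluate whether the efficacy of low-dose tamoxifen in reducing IBTR is not inferior to that of whole breast irradiation". Table 2 assumes 6% in both arms, a 5-point margin, alpha 0.05 and power 0.9, which gives 385 per arm.
- **Rationale and hypotheses, and Interim analyses:** both are framed on IBTR alone.

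**The concern.** The trial exists to settle one question: whether low-dose tamoxifen is non-inferior to radiotherapy for IBTR. The abstract and Outcomes section give all four recurrence sites primary standing. The only section on analysing the primary outcome implements them as four separate comparisons, each at 5%, and does not say which one decides the trial. Under that text, a nominally significant difference at any of the four sites could be reported as a primary result.

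The contralateral breast shows why this matters. The Background cites a hazard ratio of 0.27 for contralateral events with tamoxifen (at 20 mg/day) after breast-conserving surgery alone, and whole-breast radiotherapy here treats one side. A contralateral difference in favour of tamoxifen is therefore plausible. As written, it could be presented as a primary endpoint met even if non-inferiority on IBTR had not been shown.

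**Working it through.** **1. What the stated alpha was spent on.** The inputs are from Sample size and Table 2: event rate 0.06 in each arm, margin 0.05, alpha 0.05, power 0.90. I take S² as the sum of the two binomial variances: S² = 2 × 0.06 × 0.94 = 0.1128. Then n per arm = (Zα + Zβ)² × S² / Δ².

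- One-sided 5%: (1.6449 + 1.2816)² × 0.1128 / 0.0025 = 386.4, so 387. With z rounded to 1.64 and 1.28 it is 384.7, so 385, the plan's figure.
- One-sided 2.5%: (1.9600 + 1.2816)² × 0.1128 / 0.0025 = 474.1, so 475. This does not match.

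The 385 per arm therefore uses a full one-sided 5% on one comparison, IBTR. Nothing in it provides for other primary tests.

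**2. Error if the four sites are co-equal primaries.** Assumptions: four log-rank tests of difference, each two-sided at 5% (the Statistics section does not state the sides), and no true difference at any site.

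- Independent tests: 1 − 0.95⁴ = 0.185, or 3.7 times the nominal 5%.
- Correlated tests (equicorrelated normal statistics; the plan gives no correlations):

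| Assumed correlation | Chance of at least one false difference |
|---|---|
| 0 | 18.5% |
| 0.3 | 17.4% |
| 0.5 | 15.6% |
| 0.7 | 13.0% |
| 0.8 | 11.4% |

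- Rare events: regional and distant recurrences may be too few for the tests to reach their nominal 5%. In simulations with 405 per arm and independent sites, IBTR was set at 6%, regional and distant recurrence at 0.2% to 1% each, and contralateral at 2% to 4% (all but the 6% are my assumptions). The result was 10% to 17%.
- If tamoxifen truly lowers contralateral events, three true nulls remain: 1 − 0.95³ = 14.3% with independence.

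**3. Which error this is.** These are false claims of difference. The error in Table 2 is a false claim of non-inferiority on IBTR, for which the null is a true excess of 5 points. Extra log-rank tests at other sites leave the error of that margin test unchanged.

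**4. What keeping four primaries would cost.** Take an equal Bonferroni split, 0.05/4 = 0.0125 one-sided for IBTR (z = 2.2414).

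- Sample size for 90% power: (2.2414 + 1.2816)² × 0.1128 / 0.0025 = 560 per arm.
- Power with 385 per arm: the standard error is √(0.1128/385) = 0.01712 and 0.05/0.01712 = 2.921, so power = Φ(2.921 − 2.241) = Φ(0.680) ≈ 75%. At one-sided 5% it is Φ(2.921 − 1.645) ≈ 90%, as planned.

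**The case against.** **The article is condensed, and multiplicity is often left to the analysis plan.** That would answer a complaint that no adjustment is described. It does not answer this point, which rests on what the text fixes: four sites under a primary label, four separate analyses, and one level for all. An analysis plan would have to depart from those statements, not merely add to them.

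**Four primaries is only one reading.** This stands in part. The abstract and Outcomes wording can describe one construct with four components, Outcomes speaks of a single objective, and the Discussion refers to the primary endpoint in the singular. A composite, or IBTR alone, needs no split of alpha. But the Statistics section names no composite and does not single out IBTR, so the text does not settle the reading. The percentages are therefore conditional on the four-primary reading.

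**Stronger readings a reader might infer.**

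- *Overall survival and the subgroups belong to the same confirmatory family, so the error is far higher.* The documents do not support this. Overall survival is labelled secondary. The size and margin subgroups stand under additional analyses, where the text says only that "the subgroups of pathological features will be managed based on the primary and secondary endpoints stratified by tumor size and surgical margin status". No 5% test within each level is stated.
- *The trial's stated 5% error is tripled.* Step 3 shows that this mixes two error rates. A factor of about three also holds only for the four sites at an assumed correlation of 0.5.

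**Conclusion.** The concern holds in a limited form. The text gives four recurrence sites primary standing, analyses each separately at 5% and leaves the decisive test unnamed, while the hypothesis, sample size and interim rule rest on IBTR. On the four-primary reading, the chance of at least one false claim of difference is 18.5% with independence and about 16% to 11% at correlations of 0.5 to 0.8, or 10% to 17% under the assumed rare-event rates, against a nominal 5%. The correlations and the non-IBTR event rates are my assumptions, as are two-sided tests and no true differences. The practical risk is selective reporting of a site other than IBTR as a primary result.

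**What to change.** In the Abstract, Outcomes and Statistics sections, name the 7-year IBTR non-inferiority comparison with the 5-point margin as the single primary, confirmatory test. Give it the full alpha and state that this is one-sided 5%, the basis on which 385 reproduces. List regional, contralateral and distant recurrence as secondary alongside overall survival, reported with estimates and confidence intervals. Limit the blanket 5% sentence accordingly.

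This costs wording only and leaves 385 per arm unchanged. With 36 patients enrolled by December 2022, according to Trial status, the change would come early relative to the target of 810. The small downside is that a nominally significant result at another site can no longer be claimed as a primary result.

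If the sponsor prefers to keep four primaries, the alpha must be divided and the power for 385 per arm restated. With an equal Bonferroni split, IBTR power falls to about 75%, or 560 per arm are needed for 90%.
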